## Abstract

**Background:**

Subcutaneous immunotherapy with high dose grass pollen (typically microgram quantities) was first described over 100 years ago. This treatment suppresses allergen-induced cutaneous late responses, with lesser effects on early responses. We previously reported that repeated 2-weekly intradermal injections of grass pollen - containing approximately 7 ng of major allergen Phl p 5 – led to a progressive suppression of the allergen-induced cutaneous response, and that by the sixth injection, this was inhibited by over 90%. The purpose of this trial is to investigate the clinical efficacy of intradermal desensitisation with low doses (i.e. nanogram quantities) of grass pollen allergen for seasonal allergic rhinitis.

**Methods/design:**

The Pollen Low dose Intradermal therapy Evaluation (PollenLITE) is a single centre double-blind randomised parallel group controlled trial of the efficacy and safety of intradermal grass pollen injections plus standard treatment, versus histamine injections plus standard treatment, in adults with moderate-severe grass pollen-induced allergic rhinitis (‘summer hay fever’). A minimum of ninety adults with a history of moderate-severe persistent allergic rhinitis during the UK grass pollen season will be randomised into two equal groups to receive 7 or 8 intradermal injections of grass pollen extract (containing approximately 7 ng of major allergen Phl p 5) or histamine, before the grass pollen season. In the summer, participants will score their symptoms, medication requirements, visual analogue scores, and complete EuroQOL (EQ-5D-5 L) and mini Rhinoconjunctivitis Quality of Life Questionnaires. Global assessments will also be recorded at the end of the pollen season. Blood samples will be collected from all participants for mechanistic immune assays. Skin punch biopsies will also be collected in 40 participants selected at random from intradermal injection sites after the grass pollen season for mechanistic assays. Finally, to investigate if the desensitising effect of intradermal immunotherapy on cutaneous responses is long-lasting, all participants will be randomised to receive a follow up intradermal injection after 3, 6 or 12 months with measurement of early and late response sizes.

**Discussion:**

Randomisation began in February 2013 and the final participant will complete the trial protocol in August 2014.

**Trial registration:**

ISRCTN 78413121

EudraCT number 2012-002193-31.

## Background

Allergic rhinitis caused by grass pollen affects a quarter of the UK population [1]. Of these, around 5 million people suffer moderate-severe persistent symptoms that have an impact on quality of life, including disturbed sleep, disruption of leisure activities and impairment of performance at work/school [2]. Therefore, there is a substantial unmet need for both therapy and prophylaxis of seasonal allergic rhinitis. In the UK, subcutaneous and sublingual immunotherapy is indicated in patients with moderate-severe symptoms who fail to respond to conventional medications [3]. Immunotherapy i.e. prophylactic inoculation with grass pollen for treatment of season allergic rhinitis was first described in 1911 [4]. The conventional approach involves the regular subcutaneous administration of allergen extracts at high doses (typically microgram quantities of Group 5 grass pollen allergens) [3]. The most commonly used form of grass pollen immunotherapy is that given by injections into the tissue beneath the skin (i.e. subcutaneously) over a period of 2–3 years with increasing amounts of allergen administered weekly for 12 to 15 weeks followed by monthly maintenance injections [3]. A body of evidence, including a Cochrane meta-analysis [5], exists to support the clinical efficacy of high dose subcutaneous immunotherapy. Grass pollen allergen may also be administered at high dose as sublingual tablets or drops, an approach further supported by Cochrane meta-analysis [6]. Both subcutaneous and sublingual high dose immunotherapy have limitations: the vaccine products are expensive and the need for repeated administration in a specialist clinic (subcutaneous immunotherapy) or daily at home (sublingual immunotherapy) is associated with additional expense and/or inconvenience.

‘Proof of concept’ has been established for a novel low dose intradermal desensitisation protocol in subjects with grass pollen-induced allergic rhinitis. A feature of an intradermal allergen injection is the development of local swelling within 6 hours, and persisting for 24–36 hours. This ‘late response’ is characterised by infiltration of inflammatory cells, notably activated TH2 cells, eosinophils and basophils. We showed that six two-weekly intradermal injections of grass pollen containing only 7 ng of major allergen Phl p 5 resulted in a >90% suppression in the cutaneous late response measured after 24 hours in response to these injections [7]. Although the injection sites were alternated between left and right arms, this effect was systemic since responses were also suppressed at a distal site (the back). The magnitude of inhibition was comparable to that seen with a conventional high dose subcutaneous grass pollen vaccine [8] despite equating to over 1000-fold less allergen over the same time period. A grass pollen extract produced by the same manufacturer and given as sublingual immunotherapy delivered 20'000-fold more group 5 allergen over a 10 week period than was given in this study, but was associated with lesser inhibition of late responses, an approximate 40% reduction compared to placebo [9]. We believe that these findings provide a strong rationale for progressing to a clinical trial. The concept of therapeutic intradermal allergen inoculation is not without precedent. In 1926, Phillips, a physician working in Arizona, published a preliminary account of his uncontrolled experiences with intradermal grass pollen immunotherapy in 29 patients [10], extended to 322 patients by 1933 [11], over 90% of whom obtained “satisfactory relief”. However, no randomised controlled trial has yet addressed the efficacy of intradermal low dose allergen injections.

High dose subcutaneous immunotherapy is associated with induction of regulatory T cells (Tregs) [12-14], probably through interaction of CD4+ T cells with pro-tolerogenic dendritic cells (DC). These cells are anti-inflammatory and also induce B cell production of allergen-specific ‘blocking’ IgG antibodies. Low dose intradermal allergen desensitisation is biologically plausible: for example, intradermal injection of radiotracers in animal models results in 100-fold higher rates of drainage to regional lymph nodes than subcutaneous injection [15], potentially leading to more efficient pulsing of lymph node dendritic cells. Also, the dermis is itself an immunologically active environment, rich in Langerhans cells, dermal DC, and lymphatics [16,17]. In contrast, conventional subcutaneous immunotherapy injections target a compartment consisting mostly of connective and adipose tissue but few DC. Irrespective of whether intradermal antigen is processed by DC locally or within draining lymph nodes, we speculate that the basis of the low dose intradermal desensitisation effect is the highly efficient targeting of pro-tolerogenic dendritic cell populations leading to induction of antigen-specific Tregs.

The rationale for the laboratory mechanistic studies using skin biopsies and blood specimens is three-fold. Firstly, there is a need to establish the effects of intradermal immunotherapy on inflammatory cell responses to allergen in tissue (particularly eosinophils, basophils, mast cells and T cells). Suppression of the allergen-induced late response in the skin and nose occurs in parallel following conventional subcutaneous immunotherapy, and the underlying immunological changes within these tissues are extremely similar, if not identical [18-25]. Secondly, we shall investigate if low dose intradermal desensitisation is associated with a systemic immunological effect. We will therefore measure serum allergen-specific IgE and IgG responses and test the biological inhibitory activity of IgG antibodies with an in-house validated assay of IgE-allergen complex binding to B cells [26]. We shall also examine the effect of low dose intradermal allergen treatment on peripheral blood basophil activation in response to grass pollen stimulation ex vivo. There is also a need for exploratory studies to investigate underlying causative mechanisms. These studies will take the form of analysis of T cells expanded from skin biopsy explants in short term cultures. Finally, it is now established that both conventional high dose subcutaneous and sublingual grass pollen immunotherapy exert long-term effects that persist after treatment discontinuation [27,28]. Extended clinical trials involving three successive years of treatment show continued clinical improvement for several years after withdrawal of treatment. To definitively assess such a comparative effect on symptoms/medication use with low dose intradermal immunotherapy would therefore ideally require a prolonged five year trial. Therefore we will perform exploratory studies to investigate the persistence of the intradermal desensitisation effect. We will do this by monitoring how suppression of the skin late response induced by treatment persists over a 12 month follow up period. Therefore the participants in the active and control groups (estimated n = 45 each) will be further sub-randomised to one of three sub-groups (estimated n = 15 each). After having completed their main ‘treatment’ injections, each sub-group will subsequently receive a single follow-up intradermal injection with allergen with late response measurement after 3, 6 or 12 months. For each time point the size of late response in the group that originally received active therapy will be compared with the group that originally received the control intervention.

## Methods/design

We hypothesise that low dose intradermal grass pollen allergen immunotherapy is an effective treatment for seasonal allergic rhinitis (‘hay fever’), reducing symptoms and rescue medication requirements, and improving quality of life for hay fever sufferers.

### Primary objective

To determine if pre-seasonal low dose intradermal grass pollen allergen immunotherapy (either 7 or 8 two-weekly injections of 10 Biological Units (33.3 SQ-U)) reduces symptoms and requirements for anti-allergic drugs in seasonal allergic rhinitis during the 2013 grass pollen season compared to the control intervention (histamine only).

### Secondary objectives

To

1) Determine if this intervention is associated with improvement in quality of life compared to the control intervention, as assessed during the 2013 grass pollen season.

2) Evaluate if this is a safe and well-tolerated form of treatment.

3) Investigate immunological mechanisms associated with this form of treatment, by examining humoral and cellular responses, both in peripheral blood and in tissue.

4) Explore if the intradermal desensitisation effect is long-lived i.e. persists following cessation of intradermal injections.

### Study design

PollenLITE is a single center (UK) double-blind randomised parallel group controlled trial of the efficacy and safety of 7 to 8 pre-seasonal intradermal injections of *Phleum pratense* grass pollen extract (each containing estimated 7 ng of major allergen Phl p 5) versus histamine control (Figures 1 and 2). The study is based at Guy’s Hospital, King’s College London. A minimum of 90 participants will be recruited and randomised 1:1 to receive active or control injections before the 2013 grass pollen season, when the clinical outcome data will be collected. All participants will also have access to conventional pharmacotherapy for allergic rhinitis. All participants will be consented in accordance with the Declaration of Helsinki. The study has been approved by the London Harrow Research Ethics Committee (reference 12/LO/0941).

**Figure 1 F1:**
[figure not shown]
Study design.

**Figure 2 F2:**
[figure not shown]
Study schedule.

### Primary endpoint

Combined symptom and medication score covering the grass pollen season period of 13th May-end August 2013.

### Secondary endpoints

1. Symptom score for each participant, covering the grass pollen season period of 13th May-end August 2013.

2. Medication score for each participant, covering the peak grass pollen season period of 13th May-end August 2013.

3. Quality of life scores, as measured by the mini Rhinoconjunctivitis Quality-of-Life Questionnaire (32) and the EQ-5D-5L questionnaire, during the peak grass pollen season.

4. A Visual Analogue Score for each participant, covering the peak grass pollen season period (mid May-end Aug 2013).

5. A global evaluation by each participant, at the end of the 2013 grass pollen season, of symptoms and a comparison with previous years.

6. Number of primary care (i.e. general practitioner) visits for hay fever during summer 2013.

7. Combined symptom and medication score during the *peak* of the 2013 grass pollen season.

8. Number of medication free days covering the grass pollen season period of 13th May-end August 2013.

9. Number of symptom free days covering the grass pollen season period of 13th May-end August 2013.

10.  Individual symptoms scores (AUC) for each organ: nose, mouth, eyes and lungs.

11.  Total number of days during which prednisolone used between 13th May-end August 2013.

12.  Frequency of adverse events, including the occurrence of systemic allergic reactions.

### Secondary endpoints in mechanistic assays

1) Inflammatory cells (eosinophils, mast cells, basophils, CD4+ T cells and Foxp3+ T cells) in skin biopsies collected 24 hours after receiving an intradermal diluent (negative control) and grass pollen allergen injection in September 2013.

2) Numbers of CRTH2^pos^CD203c^pos^CD3^neg^CD303^neg^ and CRTH2^pos^CD63^pos^CD3^neg^CD303^neg^ activated peripheral blood basophils cells following in vitro activation with grass pollen allergen (Visit 7).

3) Serum concentrations of *Phleum pratense*-specific IgG, IgG1, IgG4 and IgE at Visit 1 and Visit 7. These sera will also be tested for inhibitory activity against allergen-IgE complex binding to B cells.

4) Gene expression profiles of CD4+ T cells derived from skin biopsy explants in September 2013.

5) Cutaneous allergen-induced late response size measured in December 2013 (i.e. approx. 3 months after previous intradermal injection), March 2014 (6 months) or August 2014 (11–12 months).

### Definition of end of study

The duration of the trial is 2 years. The trial will end when the last subject makes the last visit to determine the late response following the final open label follow up intradermal injection at the August 2014 time point.

### Subject selection and withdrawal

#### Inclusion criteria

1) Adults aged 18 to 65 years.

2) A clinical history of grass pollen-induced allergic rhinoconjunctivitis for at least 2 years with peak symptoms in May, June, or July.

3) A clinical history of moderate-severe persistent rhinoconjunctivitis symptoms interfering with usual daily activities or with sleep.

4) A clinical history of rhinoconjunctivitis that remains troublesome despite treatment with either antihistamines or nasal corticosteroids during the grass pollen season.

5) Positive skin prick test response, defined as wheal diameter greater than or equal to 3 mm, to *Phleum pratense*.

6) Positive specific IgE, defined as greater than or equal to IgE class 2, against *Phleum pratense*.

7) For women of childbearing age, a willingness to use an effective form of contraception for the duration of intradermal injections.

8) The ability to give informed consent and comply with study procedures.

#### Exclusion criteria

1) Pre-bronchodilator FEV1 less than 70% of predicted value at screening visit.

2) A history of seasonal grass pollen-induced asthma requiring regular treatment with salbutamol or inhaled corticosteroids. Patients with mild seasonal grass pollen-induced asthma may be included, provided symptoms are satisfactorily controlled with occasional salbutamol only.

3) A clinical history of symptomatic seasonal allergic rhinitis and/or asthma due to tree pollen or weed pollen near or overlapping the grass pollen season, although patients with mild intermittent symptoms requiring only occasional antihistamines may be included.

4) A clinical history of symptomatic allergic rhinitis and/or asthma caused by a perennial allergen to which the participant is regularly exposed, although patients with mild intermittent symptoms requiring only occasional antihistamines may be included.

5) Emergency department visit or hospital admission for asthma in the previous 12 months.

6) History of chronic obstructive pulmonary disease.

7) History of significant recurrent acute sinusitis, defined as 2 episodes per year for the last 2 years, all of which required antibiotic treatment.

8) History of chronic sinusitis, defined as a sinus symptoms lasting greater than 12 weeks outside the grass pollen season, that includes 2 or more major factors or 1 major factor and 2 minor factors. Major factors are defined as facial pain or pressure, nasal obstruction or blockage, nasal discharge or purulence or discolored postnasal discharge, purulence in nasal cavity, or impaired or loss of smell. Minor factors are defined as headache, fever, halitosis, fatigue, dental pain, cough, and ear pain, pressure, or fullness.

9) At randomisation, current symptoms of, or treatment for, upper respiratory tract infection, acute sinusitis, acute otitis media, or other relevant infectious process; serous otitis media is not an exclusion criterion. Participants may be re-evaluated for eligibility after symptoms resolve.

10) Current smokers or a history of greater than or equal to 5 pack years.

11) Previous treatment by immunotherapy with grass pollen allergen within the previous 5 years.

12) History of life-threatening anaphylaxis or angioedema.

13) Ongoing systemic immunosuppressive treatment.

14) History of intolerance of grass pollen immunotherapy, rescue medications or their excipients.

15) For females of childbearing age a positive serum or urine pregnancy test with sensitivity of less than 50 mIU/mL within 72 hours of first administration of study therapy.

16) Lactating females.

17) The use of any investigational drug within 30 days of the screening visit.

18) Ongoing treatment with leukotriene receptor antagonists, beta-blockers, calcium channel blockers, tricyclic antidepressants, monoamine oxidase inhibitors or anti-IgE monoclonal antibody.

19) The presence of any medical condition that the investigator deems incompatible with participation in the trial.

20) Individuals with insufficient understanding of the trial.

### Recruitment

Participants for PollenLITE will be identified via a recruitment campaign including advertisements in press, online and on public transport. Potential participants will be invited to visit the trial website (http://www.pollenlite.co.uk) and answer 7 pre-screening questions before registering. Participants passing pre-screening on the trial website will be contacted for further telephone screening, and if considered potentially suitable will be invited to attend the Clinical Research Facility at Guy’s Hospital for a formal screening visit. A Participant Information Sheet will be provided to each person to read prior to the screening visit. At the screening visit (Visit −1), there will be an opportunity to ask questions of a staff member trained in all trial procedures, as formally delegated by the PI. Written informed consent will be obtained by a physician prior to screening and any other study specific procedures taking place. The original signed consent form will be retained in the Investigator Site File, with a copy filed in the participant’ s hospital records, and a further copy provided to the participant. Individuals will be free to decline further participation without giving reasons. The screening visit will comprise a full medical and allergic history, skin prick testing to a panel of common inhalant allergens, recording of concomitant medications, limited physical examination, measurement of vital signs, spirometry and collection of a venous blood sample for total and *Phleum pretense*-specific IgE levels and for storage for serum based mechanistic assays (baseline sample). For participants who either do not meet the eligibility criteria at the screening visit or decline to proceed further, reasons for non-participation will be recorded where known. The history and test results of every potentially eligible participant will be reviewed by the PI before an appointment is made for Visit 1 (randomisation and first injection). To ensure that a minimum of 90 participants is randomised, up to 100 screened participants will be booked for visit 1, allowing for a 10% drop-out rate between screening and randomisation. In the event that more than 90 eligible participants attend for visit 1, all will be included in the study and randomised up to a maximum of 100. All female participants of childbearing age will be required to undergo a urine pregnancy test with sensitivity of less than 50 mIU/mL within 72 hours of randomisation and first administration of study therapy at Visit 1.

### Trial medication

The active drug will be 10 Biological Units (BU) (33.3 SQ-U) of *Phleum pratense* soluble grass pollen extract (Aquagen SQ Timothy, ALK Abello, Reading UK) contained in a 20 microliter volume (i.e. 500 BU/ml (1666.7 SQ-U/ml)). Individual vials for each participant and each visit will be pre-prepared and pre-labeled by Guy’s Hospital Pharmacy under GMP conditions. In brief, Aquagen SQ Timothy Grass Pollen extract will be reconstituted in manufacturer-supplied diluent to the maximum recommended concentration (30'000 BU/ml (100'000 SQ-U/ml) i.e. 60-times final working strength; shelf life 6 months at 2-8°C after reconstitution) and 0.15 ml aliquoted into glass study vials. At each visit for intradermal injection the investigator will add 8.85 ml of clinical grade 0.9% normal saline at ambient temperature to the vial corresponding to that participant’s visit to achieve a 60-fold dilution. Twenty microliters will then be aspirated from this vial and administered directly. The allergen requires dilution on the day of administration as the recommended shelf life of Aquagen SQ Timothy Grass Pollen extract at 500 BU/ml (1666.7 SQ-U/ml) is only 14 days. Control drug will be histamine only, administered at a concentration of 100 mcg/ml. To help preserve blinding, histamine concentrations will be reduced to 30 mcg/ml for the 3^rd^ and 4^th^ injections, and 10 mcg/ml for 5, 6 and 7^th^ injections. To match the grass pollen extract dilution and preserve blinding, histamine will also be aliquoted into study vials at 60-times final working strength in 0.15 ml volumes, for further dilution with 8.85 ml of clinical grade 0.9% normal saline immediately prior to injection. Active and control study medications will appear identical.

Following manufacture, vials will be packed into individual dispensing packs that will be dispensed by pharmacy against a single study prescription for each study participant, covering all visits. At randomisation, an email will be sent from the randomisation system to the dispensing pharmacy. On receipt of a study prescription, the pharmacist will refer to this email to select an appropriate pack of active or control medication. The pack will then be fully blinded and dispensed. The blinded dispensed packs will thereafter be stored in the Clinical Research Facility in temperature monitored fridges in a secure environment.

### Dosing regimen

A series of 7 intradermal active or control injections will be administered 2-weekly into the forearm between before the 2013 grass pollen season. The first injection will be administered between 18th February and 1st March 2013. We will aim to administer the 7th injection between 13th May and 24th May 2013. The injection site will again be alternated between left and right arms at each visit. Intradermal injections will be administered in a 20 microliter volume using a 29 gauge insulin syringe (Becton Dickinson Micro-FineTM). As a precaution against systemic allergic reactions all subjects will be observed for one hour after the first injection, and for 30 minutes after subsequent injections, in a clinical area with full resuscitation facilities.

Occasionally an injection may be administered too deeply (into subcutaneous tissue) resulting in failure to generate an immediate injection ‘bleb’ and subsequent characteristic wheal. For this reason, the injection site will be inspected in all subjects 15 minutes after each injection to confirm successful intradermal injection. In the absence of the typical wheal, the injection will be repeated at 1 cm from the original site.

In the event of acute illness (e.g. upper respiratory tract infection) or other unforeseeable circumstance, administration of active/control intervention may be postponed up to a maximum of 3 weeks since the previous injection, at the discretion of the investigator. The study team aim to perform over 90% of injections at 12–16 day intervals, although in exceptional circumstances the minimal interval permitted between injections may be reduced to 7 days. Onset of symptoms associated with the London grass pollen season generally falls between late May - early June. Therefore, if schedule adjustments result in a participant completing their 7 injections before 13th May 2013, the 7th injection will be repeated 12–16 days later in late May.

Following these injections, clinical outcomes will be measured during the summer of 2013. In September 2013 and either 3, 6 or 12 month later, all participants will also receive intradermal injections with diluent (negative control) or 10 BU (33.3 SQ-U) of grass pollen allergen. Although the trial will not be unblinded at this stage, these intradermal injections will be open label.

Most participants will not be taking antihistamines at the time of intradermal injections since these will be performed before the grass pollen season. Nevertheless all participants will be asked to avoid taking antihistamines for 5 days before receiving an intradermal injection so that the presence of a wheal can be confirmed. Following an intradermal injection participants may take an antihistamine to reduce the local itching and swelling. If they wish to do so before leaving the clinical research facility an antihistamine tablet will be provided. The exception will be visits 10 and 11, when cutaneous response sizes will be measured and therefore participants will be asked to refrain from taking an antihistamine. Any oral steroids must be stopped for a minimum of 2 weeks before the intradermal injection in September 2013 since this may interfere with late response measurements and skin biopsy studies. Participants will be asked to refrain from alcohol consumption on the same day before and for 2 hours after an intradermal injection.

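### The 3, 6 and 12 month persistence times run from a September 2013 open-label injection given to all participants, not from the end of treatment in May, so they measure durability after a further dose

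*Protocol article*

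**What the plan says.** Secondary objective 4 is to "Explore if the intradermal desensitisation effect is long-lived i.e. persists following cessation of intradermal injections". The Background ties this to the end of the main treatment injections and says that "each sub-group will subsequently receive a single follow-up intradermal injection with allergen with late response measurement after 3, 6 or 12 months". It mentions no other allergen injection between the treatment course and that follow-up.

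The Dosing regimen section dates the end of the course: "We will aim to administer the 7th injection between 13th May and 24th May 2013". A repeat injection in late May is allowed for anyone who finishes early. The same section then says: "In September 2013 and either 3, 6 or 12 month later, all participants will also receive intradermal injections". It describes the content as "with diluent (negative control) or 10 BU (33.3 SQ-U) of grass pollen allergen" and adds that "these intradermal injections will be open label".

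Under Secondary endpoints in mechanistic assays, item 5 is "Cutaneous allergen-induced late response size measured in December 2013 (i.e. approx. 3 months after previous intradermal injection", followed by March 2014 for 6 months and August 2014 for 11–12 months. Item 1 of that list has skin biopsies taken "24 hours after receiving an intradermal diluent (negative control) and grass pollen allergen injection in September 2013".

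The Secondary efficacy parameters and Statistical analysis sections compare the original active arm with the original control arm at each of the three time points.

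**The concern.** The Background and objective 4 lead a reader to expect time since treatment ended. The dosing and endpoint sections start the clock about four months later, at an injection that appears to be allergen and is the same size as a treatment dose (10 BU, Trial medication section). On that schedule the active arm reaches every listed persistence time point with one more dose than its course, and the control arm has had its first intradermal trial dose of allergen.

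This bears on interpretation because the protocol's own premise is progressive suppression with repeated low doses (Abstract) and an effect that is systemic rather than confined to the injected site (Background). Using a different site therefore does not rule out carry-over. At stake is the wording of the conclusion on objective 4: a result labelled 12 months could be reported as 12 months off treatment, which this schedule cannot show.

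**Working it through.** **Step 1. Is the September injection allergen, and for everyone?**

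- The Dosing regimen section gives the September injections to all participants but joins diluent and allergen with *or*. Item 1 of the mechanistic endpoints joins them with *and*, although that item concerns biopsies, which 40 participants undergo (Randomisation section).
- The Dosing regimen section also requires oral steroids to be stopped before the September injection, because they could interfere with late response measurement as well as with the biopsy work. A late response to allergen is therefore expected in September.
- The same section says that cutaneous responses are measured at visits 10 and 11. The section on procedures for secondary efficacy parameters has quality-of-life forms, the last dated 4 September 2013, collected at visits 8, 9 and 10. Visit 10 is then the September visit and visit 11 the later follow-up.

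Allergen for all participants in September is the likely reading. It remains an inference, because the schedule figure is not available to check.

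**Step 2. Reproduce the stated intervals.** Months = days / 30.4375, using calendar mid-points, with time zero at 15 September 2013:

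- to 16 December 2013: 92 days = 3.0 months
- to 16 March 2014: 182 days = 6.0 months
- to 16 August 2014: 335 days = 11.0 months (range 10.0–12.0 over all dates in the two months)

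These match the stated 3, 6 and 11–12 months, so the endpoint dates fit a September time zero.

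**Step 3. Recount from the end of treatment.** The central value runs from 18 May 2013 to mid-month. The shortest interval runs from 24 May to the first day of the month, and the longest from 13 May to the last day.

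| Measurement | Central | Shortest | Longest |
|---|---|---|---|
| December 2013 | 212 d = 7.0 mo | 191 d = 6.3 mo | 232 d = 7.6 mo |
| March 2014 | 302 d = 9.9 mo | 281 d = 9.2 mo | 322 d = 10.6 mo |
| August 2014 | 455 d = 14.9 mo | 434 d = 14.3 mo | 475 d = 15.6 mo |

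A repeat injection as late as 28 May (12 May plus 16 days) would shorten the lower limits by 4 days, about 0.1 month. Counted from May 2013, 3, 6 and 12 months would be about August 2013, November 2013 and May 2014.

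**Step 4. Place the September measurement.** 24 May to 1 September is 100 days = 3.3 months; 13 May to 30 September is 140 days = 4.6 months. No allergen injection is scheduled between the end of the course and this measurement.

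**Step 5. Count doses before each later measurement.** The active arm has had 8–9 allergen doses instead of 7–8, an increase of 1/8 to 1/7 (12.5% to 14%). The control arm has had 1 instead of 0.

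**The case against.** The time origin is disclosed. Item 5 of the mechanistic endpoints counts from the previous intradermal injection and gives calendar months, so that definition is not itself wrong. Only the Background is loose, and its wording could mean one randomised time point per sub-group. This is fair, but the Background still places the follow-up after the main treatment course with no intervening dose, and the Secondary efficacy parameters section gives the 3, 6 and 12 months without an origin.

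A late response cannot be measured without injecting allergen, the September injection serves the tissue endpoints, and sub-randomisation limits each participant to one later challenge. All of this stands, and nothing here argues for removing an injection.

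A reader might infer that the re-dosing invalidates or biases the comparison between arms. The documents do not support that. Both arms receive the same September procedure, so the contrast remains randomised; what changes is the question it answers. The protocol already treats 7 and 8 injections as one regimen, and its suppression data come from repeated two-weekly dosing. It gives no figure for the effect of one isolated dose, or for how long such an effect lasts. An extra dose could sustain suppression in the active arm, and a first dose could begin it in controls, but neither size nor net direction can be derived.

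The endpoint is also exploratory, and the primary endpoint (13 May to end of August 2013) is unaffected. That limits the weight of the point without removing it.

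**Conclusion.** The point holds as one of time origin and interpretation. The Background conflicts with the Dosing regimen section and the mechanistic endpoint list. On the likely reading of the September visit, every listed persistence time point follows one further treatment-size allergen dose in both arms and falls about 7.0 (6.3–7.6), 9.9 (9.2–10.6) and 14.9 (14.3–15.6) months after the last treatment injection. The results will estimate durability after an additional dose, not persistence at 3, 6 and 12 months off treatment.

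This rests on the planned injection dates of 13–24 May 2013, on any date within each named month for the later visits, and on the inference that all participants receive allergen in September.

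It would go too far to conclude that the later comparisons cannot be reported, or that the September comparison should replace them. They remain valid randomised comparisons and are the only long-term information on an objective that asks whether the effect is long-lived.

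**What to change.** 1. Reconcile the Background with the Dosing regimen section and the mechanistic endpoint list on the number and timing of post-treatment injections. Reconcile the *or* and *and* descriptions of the September injection's content.
2. State time zero for the persistence endpoint wherever 3, 6 and 12 months appear, and report each participant's actual time since the last treatment injection.
3. Add the September 2013 comparison between arms of late response size as a pre-specified persistence time point. It alone precedes the further dose, and the text indicates that the measurement is already taken.
4. Keep the December, March and August comparisons, and describe them as following one additional open-label allergen injection in both arms.

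None of this changes a visit, an injection or the sample size. The Statistical analysis section has the analysis plan finalised before database lock, so the plan can carry items 2 to 4. The cost is a more qualified long-term claim for an exploratory endpoint: the estimate free of an intervening dose reaches only about 3.3–4.6 months after treatment.
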